### Strategies to improve adherence to interventions {11c}

We have applied several strategies to improve adherence to the intervention. We will have supervised exercise sessions, and use exercise diaries to track the patient progress. The patients can keep the wrist-worn heart rate monitor/fitness tracker at the end of the study as a gift for completing follow-up.

### Relevant concomitant care permitted or prohibited during the trial {11d}

The patients enrolled in the study will receive relevant concomitant care during the entire study period regardless of being randomized to the interventional arm or comparator arm.

### Provisions for post-trial care {30}

All participants included in the study will be informed of the patient's rights when included in a trial. In case of any unintended harm to the participants in the study during the intervention, they will have the right to compensation defined by Danish legislation (Patienterstatningsordningen). Patients may choose to withdraw at any time.

### Outcomes {12}

The primary outcome was chosen in collaboration with our patient representatives connected to this study, and because the health-related quality of life is a multidimensional measure incorporating the patient life situation. The secondary outcomes were chosen to reflect the overall general health status of the patient as well as the non-disease specific quality of life, where the explorative outcomes focus on changes in the immune system.

### Primary outcome

We will use the Danish version of the IBDQ [40].IBDQ

### Secondary outcomes

Waist circumferencesClinical disease activity:i.HBIii.SSCAIBlood pressureLipid status:i.Low-density lipoprotein (*LDL)*ii.High-density lipoprotein (*HDL)*iii.Triglyceridesiv.Total cholesterolTotal cholesterol = LDL+ HDL + (20% of the total triglycerides)v.Hemoglobin A1cEQ5D-5L (not disease-specific) [41]

#### Explorative outcomes

Biomarkers:i.Fecal calprotectinii.C-reactive proteinImmunology, biomarkers (Panel - cytokines):i.Interleukin 6 ii.Interleukin 8 iii.Interleukin 10 iv.Tumor necrosis factor alpha 

The outcomes regarding the quality of life are measured at baseline and week 12, whereas the disease scores and biomarkers are measured in weeks 0, 4, 8, and 12. We will analyze blood and stool samples at baseline, 4, 8, and 12 weeks. The analyses are carried out within 5–7 days after the samples are collected, except for the analysis of cytokines which are analyzed at the end of the study.

### Participant timeline {13}

**Table Tabb:** 

**Timepoints**	**Study period**				
	**− t1**	**t0**	**t1**	**t2**	**t3**
	**Pre-study**	**0**	**4 weeks**	**8 weeks**	**12 weeks**
**Eligibility** Pre-screening	X				
Inclusion/exclusion	X				
Informed consent	X				
Allocation (randomization)	X				
**Outcome** *General health* Waist circumference Blood pressure Disease activity (HBI + SSCAI)		X X X			X X X
*Blood and stool samples* C-reactive protein Fecal calprotectin Lipid status Cytokines		X X X X	X X X X	X X X X	X X X X
*Health-related quality of life* IBDQ EQ5D		X X			X X
*Activity monitoring* Accelerometer (AX3)	X				X
**Interventions** Exercise intervention		X	X	X	X
Online lesson		X			

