**Methods:**

We will apply a superiority design in this open-label randomized clinical trial including 150 patients equally allocated to intervention and usual care. The intervention will be based on a 12-week aerobic exercise program and will include two supervised exercise sessions of 60 min per week, combined with one weekly home training session. We have defined a moderate exercise level as 60–80% of patients’ maximum heart rate. The patients in the intervention group will also be offered an online video lesson of 15–25 min on lifestyle guidance, and the same online video lesson will be offered in the comparator group. Questionnaires on quality of life will be forwarded electronically both at inclusion and at the end of the study, and the patients will have blood samples, and fecal samples for calprotectin at baseline, weeks 4 and 8, as well as after 12 weeks (study end).

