## Interventions

### Explanation for the choice of comparators {6b}

We include patients with Crohn’s disease and ulcerative colitis with moderate disease activity as comparators and offer them one online lesson of 15–25 min on lifestyle guidance including general advice on healthy living. Specialized health personnel will present an educational video lesson. The patients in the comparison arm will receive the usual medical treatment with regular follow-up in the outpatient clinic. In this group, we will also monitor 7 days of physical activity level by accelerometry using the AX3 accelerometer [Axivity Ltd., Newcastle upon Tyne, UK] in weeks 0 and 12. The comparators have been chosen to represent the usual treatment and to help determine the efficacy of the intervention. Furthermore, all patients in the comparison arm will receive a wrist-worn heart rate monitor/fitness tracker (commercial) after completing a follow-up program identical to the patients in the intervention arm.

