### Implementation {16c}

The research nurse will generate the randomization at inclusion and according to the randomization, patients will be assigned to either the intervention arm or the comparison arm.

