## Assignment of interventions: blinding

### Who will be blinded {17a}

This study includes an exercise intervention that does not allow for the blinding of the participants or the healthcare personnel involved in the study.

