## Discussion

This trial is the first trial trying to include a large number (*n* = 150) of patients with IBD and moderate disease activity in order to explore the effect of an exercise intervention. We have chosen this number of patients to be able to evaluate meaningful effects in our specified outcomes. We expect that the results will be helpful in future clinical guidelines, and add highly relevant knowledge on the effect of exercise that may guide patients in clinical practice and may provide a new patient-active disease management approach. The current evidence on the effects of exercise on IBD is inconsistent with few clinical trials with a sufficient number of included patients.

The randomized controlled study design applied in our trial is a strength. Another strength related to this trial is that the protocol has been developed with guidelines from the SPIRIT and PREPARE guidelines, [30, 49] and that the protocol is being published to enhance clearance and transparency. Further strengths in the development of the protocol are that patient representatives were involved to help inform plus guide the selection of outcome of interest, design exercise regime using the FITT principles, [26] and online lifestyle presentation. Another strength is that the measurements in the trial are based on validated questionnaires in combination with objective repeated measurements, e.g., accelerometry, blood samples, and fecal samples that are stored in a biobank to evoke current and future relevant research.

Our trial has some limitations. Due to the nature of the exercise intervention blinding the research nurses, physiotherapists, and participants is not an option. Limitations according to the recruitment of participants do exist because we focus on patients with mild to moderate disease activity. These patients may be more cautious to participate due to symptoms or because of the possibility of not being randomized to the intervention or not being able to participate in the intervention because of their schedule. Another limitation of the trial is that we have not planned follow-up after week 12. However, we have chosen not to plan a long-term follow-up because we do not yet clearly know the short-term effect of exercise, which is the focus of this trial. Selection bias may be of concern when conducting a trial on exercise, and this may influence the generalizability of the study.

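### The participant timeline puts randomisation before the baseline IBDQ, EQ5D and disease scores, and nothing in this open-label protocol says they are completed first

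*Protocol article*

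**What the plan says.** - **Participant timeline {13}.** The row "Allocation (randomization)" has its mark in the pre-study column (−t1). The row "Health-related quality of life* IBDQ EQ5D" is marked at week 0 and week 12 only, as is the row "Waist circumference Blood pressure Disease activity (HBI + SSCAI)". Blood and stool samples start at week 0. The exercise intervention and the online lesson also start in the week 0 column.
- **Implementation {16c}.** "The research nurse will generate the randomization at inclusion and according to the randomization, patients will be assigned" to one of the two arms. Concealment mechanism {16b} describes a randomisation button and states no condition for using it.
- **Abstract, Methods.** "Questionnaires on quality of life will be forwarded electronically both at inclusion and at the end of the study". Data management {19} adds that surveys go to the patient's electronic mailbox.
- **Who will be blinded {17a}.** The intervention "does not allow for the blinding of the participants or the healthcare personnel involved in the study".
- **Statistical methods {20a} and Sample size {14}.** The outcomes are compared between groups from baseline to week 12, by t-test or Wilcoxon rank-sum test for the primary outcome. The trial is sized on a 13.8-point difference in IBDQ change with SD 25.
- **Accelerometry.** The comparator section {6b} describes monitoring "using the AX3 accelerometer [Axivity Ltd., Newcastle upon Tyne, UK] in weeks 0 and 12", and the intervention section {11a} gives the same weeks. The timeline marks the first measurement at −t1. Additional analyses {20b} use baseline accelerometry to form strata.

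**The concern.** A baseline is a safe starting point for a change score only if allocation cannot influence it. Here the one place that orders the two events puts allocation first, and the patient who fills in the questionnaire knows the arm. The primary outcome is the week-12 score minus that baseline, so half of it would be open to a reaction to the allocation.

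The exposed measures are those that depend on what the patient reports: IBDQ, EQ5D and the symptom-based HBI/SCCAI. Waist and blood pressure, taken by unblinded staff, are less exposed. Lipids, cytokines, CRP and calprotectin are hardly exposed at all. If disease severity at baseline, a planned stratifier, is taken from the t0 HBI/SCCAI, that stratifier follows allocation too.

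**Working it through.** **Order of events.** Set side by side:

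| Source | Randomisation | Baseline IBDQ |
|---|---|---|
| Participant timeline {13} | −t1 | t0 |
| Implementation {16c} | at inclusion | not mentioned |
| Abstract, Methods | not mentioned | sent at inclusion |
| Additional consent provisions {26b} | not mentioned | not among the eligibility data recorded after consent |

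The text leaves the order open. The table fixes it, with allocation first. Because the questionnaire is sent electronically, the date of sending is also not the date of completion.

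**The plan's own sample size.** Inputs from Sample size {14}: difference 13.8, SD 25, power 80%, alpha 0.05 (taken as two-sided). The two-sample t-test calculation gives 52.5, so 53 per arm and 106 in total, with power 0.804. The stated 106 reproduces, so the sample size is not at issue here.

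**Direction.** Take a higher IBDQ score as better. Let s0 and s12 be the differences between arms (exercise minus comparator) in reporting caused by knowing the arm, at baseline and at week 12. The bias in the change contrast is s12 − s0.
- Disappointed comparators lower the comparator baseline, so s0 > 0.
- Optimistic exercisers raise the exercise baseline, so s0 > 0.

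Both mechanisms make the bias negative, against exercise, unless s12 is as large as s0.

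**Size, as an illustration.** The documents give no figure for s0. Assume s0 = 2, 3 or 5 and s12 = 0. Analysed patients: 75 × (1 − 0.33) ≈ 50 per arm. SE = 25 × √(2/50) = 5.0. Two-sided t-test power at the reduced difference:

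| Assumed shift | Share of 13.8 | Difference left | Power, 50 per arm |
|---|---|---|---|
| 0 | 0% | 13.8 | 78% |
| 2 | 14% | 11.8 | 65% |
| 3 | 22% | 10.8 | 57% |
| 5 | 36% | 8.8 | 41% |

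With the plan's 53 per arm (SE 4.86, normal approximation) power goes from 81% to 68%, 60% and 44%, so the pattern does not depend on the choice of 50.

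**The case against.** Several objections carry weight.

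- **The table is thin evidence of sequence.** Its pre-study column is broad and it is loosely drawn: it omits the week 4 and 8 disease scores that the Outcomes section {12} schedules, and it disagrees with the text on accelerometry. Practice may have been baseline first. This stands as a limit on certainty. It does not remove the point, because no section states the safe order.
- **Some values precede allocation in any case.** Disease score and calprotectin or CRP are eligibility criteria and are recorded after consent, so values of these from before allocation exist. This stands, and it narrows the point to IBDQ, EQ5D and the repeated outcome scores at t0.
- **A persisting shift cancels.** Patients are equally unblinded at week 12, and whatever part of the shift remains then drops out of the change score. This stands. The power figures are for the case in which none of it persists.
- **Missing baselines are provided for.** The missing-data section {20c} plans multiple imputation, a complete-case comparison and best/worst sensitivity analyses, so patients lost between allocation and baseline are not left without a method.

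A reader might infer that a baseline taken after allocation inflates the false-positive rate in favour of exercise. The documents give no mechanism for that. The two natural reactions push the other way: with SE 5.0 and no true effect, shifts of 2, 3 and 5 points lower the chance of wrongly declaring exercise superior from 2.5% to about 0.9%, 0.5% and 0.15%. A reader might also take the Discussion's remark on "the possibility of not being randomized to the intervention" as evidence of biased reporting. That sentence concerns caution about joining the trial and says nothing about how baseline questionnaires are answered. Nor does any section show that the baseline accelerometer week falls after exercise has begun.

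**Conclusion.** The point holds in limited form. Followed as written, the timeline has patients report the baseline of the primary outcome after allocation in an unblinded trial, and no other section corrects it. What is established is an unsafe or, at best, unstated order. That the baseline was in fact distorted is not established.

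The likely direction is against exercise, so the risk is a diluted effect and lost power. The fall from about 78% to between 65% and 41% rests on an assumed shift of 2 to 5 points, none of it present at week 12, SD 25 and 50 analysed per arm. Any persistence makes the loss smaller. Laboratory outcomes and the sample size are not called into question.

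The accelerometry discrepancy (−t1 against week 0) is separate and smaller. It matters because that measurement is a planned baseline stratifier, although it is not a listed outcome.

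**What to change.** 1. **Protocol.** In the timeline, move the allocation mark after the t0 assessments, and state in Implementation {16c} that randomisation follows a completed baseline.
2. **Database.** Open the REDCap randomisation button only once baseline IBDQ, EQ5D and HBI/SCCAI are complete, and preferably waist and blood pressure too.
3. **Patients already enrolled.** Trial status gives an inclusion end of 1 May 2023, so re-sequencing may no longer be possible. Compare each patient's baseline IBDQ completion date with the randomisation date. If baseline came first throughout, correct the table and no more is needed. Where it came after allocation, report how often and in which arm, and add a sensitivity analysis of week-12 IBDQ that does not use that baseline. Adjusting for the post-allocation baseline is not a substitute: at an assumed correlation of 0.5 it would remove only about half of the bias. The week-12 analysis still carries any reporting shift present at week 12, so it should be read beside the change-score result and not in place of it.
4. **Accelerometry.** Reconcile the timeline with sections {6b} and {11a}, and state whether the baseline week precedes allocation.

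The cost is a form dependency and some wording, slightly later randomisation, and the loss of patients who never complete baseline, who would not be randomised. The 106 and 150 do not change.

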#### Sample size {14}

To calculate the number of patients needed in this trial, we have used a power of 80% and an alpha level of 5% (0.05) and used outcome differences observed in previous studies. We need to include at least 106 patients, with 53 patients in the intervention arm and 53 in the comparison arm to be able to detect a clinically relevant 13.8 (SD ± 25) mean difference in change between the groups on the IBDQ scale based on the similar changes observed in studies by Ng, Millard [12] and Klare, Nigg [9]. A minimum clinical important difference (MCID) for the IBDQ has previously been reported as an absolute change of 16 points in patients with Crohn’s disease; however, MCID for the IBDQ is not clearly defined [42]. We have performed a power analysis on the secondary and explorative outcomes, not reported, and overall we need to include a total of 100 patients in these analyses. Based on this, and to cover all outcomes including 33% drop-out, we have estimated a total study size of 150 patients, with 75 in both the intervention arm and the comparator arm.

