## Assignment of interventions: allocation

### Sequence generation {16a}

We will use a 1:1 computer-based randomization module embedded in RedCap provided by OPEN using computer-generated random numbers and in blocks of four.

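### The 150 patients do not cover the 106 required for the IBDQ at the stated 33% drop-out: a minor inconsistency in the sample size paragraph

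*Protocol article*

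**What the plan says.** All the figures stand in one paragraph of the protocol article, Sample size {14}.

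- **Primary outcome.** "We need to include at least 106 patients, with 53 patients in the intervention arm and 53 in the comparison arm". This is for 80% power at a 5% alpha level, to detect a "clinically relevant 13.8 (SD ± 25) mean difference in change between the groups on the IBDQ scale".
- **Secondary and explorative outcomes.** A separate power analysis, whose details are not reported, leads to the statement that "overall we need to include a total of 100 patients in these analyses".
- **Total.** The paragraph ends by saying that "to cover all outcomes including 33% drop-out, we have estimated a total study size of 150 patients". The split is equal, at 75 per arm.

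Sequence generation {16a} confirms equal allocation. Two further sections bear on what a drop-out costs. Plans to promote participant retention and complete follow-up {18b} says that patients who withdraw, in either arm, will be asked whether they would still answer the electronic questionnaires or attend visits. Section {20c}, on non-adherence and missing data, plans multiple imputation in the intention-to-treat analysis.

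**The concern.** The primary outcome is one of the outcomes that the total is said to cover. The 106 must therefore survive the 33% allowance, and it does not. The paragraph makes three statements (106 needed, 33% allowed for, 150 enough) that cannot all be true.

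This matters because it is the only justification given for the size of the primary comparison. A reader would take from it that the trial keeps 80% power for the IBDQ with a third of patients lost. The printed figures do not support that drop-out tolerance.

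**Working it through.** **Inputs, all from Sample size {14}:** difference in change 13.8; SD 25, read as the SD of the change within each arm; alpha 0.05; power 80%; drop-out 33%; total 150, 75 per arm. The paragraph does not say whether the test is one- or two-sided. I take it as two-sided, because a one-sided test needs 41 per arm and does not match the printed 53.

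**Step 1. Reproduce the 106.** The standardised difference is 13.8 / 25 = 0.552. A two-sample t-test at two-sided 5% with 80% power needs 52.5 per arm, so 53 per arm and 106 in total. This matches the plan exactly. The normal approximation gives 52 per arm, 104 in total. The 106 is therefore a number of analysed patients, before any allowance for drop-out.

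**Step 2. Take 33% from 150.** 150 × (1 − 0.33) = 100.5, or 100 if the allowance is exactly one third. That is about 50 per arm, six patients below 106.

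**Step 3. Find which requirement leads to 150.** The correct inflation is n / (1 − d); the common shortcut is n × (1 + d).

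| Starting number | n / 0.67 | n × 1.33 |
|---|---|---|
| 106 (IBDQ, t-test) | 158.2, so 159 (160 with equal arms) | 141.0 |
| 104 (IBDQ, normal approximation) | 155.2, so 156 | 138.3 |
| 100 (secondary and explorative) | 149.3, so 150 | 133.0 |

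Only the 100 leads to 150. Neither formula takes 106 to 150, and using the slightly smaller normal-approximation requirement does not close the gap.

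**Step 4. Find the loss that 150 can bear.** 1 − 106/150 = 0.293. So 44 patients can be lost before the number falls below 106, against about 50 at 33%.

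**Step 5. Power for 13.8 points, SD 25, two-sided 5%.**

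| Evaluable per arm | t-test | Normal approximation |
|---|---|---|
| 53 | 80.4% | 81.1% |
| 50 | 78.0% | 78.8% |

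Section {20a} allows a Wilcoxon rank-sum test if the data are judged non-parametric. On normally distributed data, with its usual efficiency of 3/π, power would be about 76% at 50 per arm and 78.5% at 53. The cost of the six missing patients is much the same with either test, about 2.4 points.

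**The case against.** The strongest case on the other side is one of proportion. Power falls from 80% to about 78%, and the tolerable loss from 33% to about 29%. No estimate, test or type I error rate depends on the sentence. The 33% is a planning allowance and not an observed rate, and the precision actually reached will show in the planned 95% confidence interval. All of this stands, and it is why the point is minor.

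The second argument is that a drop-out need not be a lost IBDQ. The questionnaire goes to the patient electronically (Data management {19}), {18b} plans to ask for it after withdrawal, and {20c} keeps patients with missing data in the analysis through imputation. This stands in part. It makes the power loss conditional on drop-outs giving no week-12 IBDQ. It does not repair the sum: the paragraph itself uses the 33% to inflate an analysed number, and imputation does not in general restore the lost information.

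Three stronger readings are tempting, and the document does not support them:

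- *The trial is underpowered, or misses 80% outright.* That holds only at a loss of about 30% or more, and then by about two points at the stated allowance.
- *The 33% was applied to the wrong requirement.* The numbers fit this, but the power analysis behind the 100 is not reported, so it remains an inference.
- *Baseline adjustment would make good the loss.* With equal variances at both times, adjustment multiplies the variance of the change-score comparison by (1 + r)/2. The 52.5 per arm then falls to 50 only if the baseline to week-12 correlation r is below about 0.9 (50/52.5 = 0.952; 2 × 0.952 − 1 = 0.905). The document gives no value for r.

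**Conclusion.** The concern holds as a minor internal inconsistency. The figure of 106 is sound. The statement that 150 covers every outcome at 33% drop-out is wrong for the primary outcome, because about 100 patients would remain. No other section of the article reconciles the figures.

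The power shortfall, about 78% against 80%, rests on four assumptions: loss reaches the full 33%; patients who drop out provide no week-12 IBDQ; the difference and SD are as planned; and the test is a two-sided t-test. If loss stays at or below about 29%, the planned power is kept with 150 randomised.

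**What to change.** Keep 150 and restate the claim in Sample size {14}, for example: *150 randomised gives 106 evaluable patients and 80% power for the IBDQ if loss of the week-12 IBDQ is at most 29%; at 33% loss (about 100 evaluable) power is about 78%.* State in the same place that the test is two-sided.

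The cost is one sentence and a slightly less favourable stated tolerance. The analysis does not change. Keeping both 33% and 80% would take 159 randomised, or 160 with equal arms. That is hardly practical by the article's own dates: Trial status gives inclusion as extended to 1 May 2023, and the article was published on 20 November 2023. A shortfall of two points does not call for more patients.
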